#### **3.2 Secondary outcomes:**

1. The pharmacokinetics of LPV/r in combination with two doses of RBT determined by the  $AUC_{0-12}$ .
2. The tuberculosis cure determined by sputum smear examination in line with the National TB Programme Guidelines
3. Proportion of participants with any grade 3 or 4 AE or SAE.

### **4. Sample size:**

Based on the  $AUC_{0-24}$  for RBT determined in previous studies (19) it was estimated that a sample size of 12 participants has a power of 80% to detect a 20% difference between the mean  $AUC_{0-24}$  for the participants taking RBT without ARV and the  $AUC_{0-24}$  for RBT combined with the various ARV. To provide a target of 12 evaluable patients in each arm (24 patients in total), because patients with low CD4 counts liable to be recruited into this study may have high mortality and morbidity, resulting in a high attrition rate, we propose a maximum of 32 patients may be enrolled (16 per arm). These additional subjects will allow a comparison of pharmacokinetic parameters between patients initiating high dose RBT with those initiating low dose RBT, and sufficient power to detect any sequence effect.

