### 5.4 Follow-up procedures:

In the Vietnamese TB Control Programme, patients come to District TB Units (DTU) every day to receive anti-TB drugs under the supervision of health workers. All patients involved in the study will come to the Outpatient Clinic at PNT Hospital to take their drugs, to receive specific training on HIV and TB as well as scheduled appointments. PNT Hospital will hold this organization according to the requirements of the study. Those who miss their scheduled appointment will be contacted within 24 hours or a home visit made to obtain information on their condition. Participants will be asked to return after 14 days

After fourteen days of RBT therapy, patients will return and will undergo the **first pharmacokinetic analysis (PK1)** as described below, as well as safety bloods and clinical evaluation. After completion of PK1 analysis, all participants will commence their randomized RBT-ART combination according to prior randomization.

1. After 3 weeks of ART, patients will complete a week 5 visit (visit 3) corresponding to **PK2** and then switch RBT doses. After a further 3 weeks of ART, patients will complete a week 8 visit corresponding to **PK3**. After completion of PK3, all participants will be referred to national program to complete SCC and continue ART according to standard program care. At the end of tuberculosis treatment, patients will have a blood taken for haematological and biochemical tests, HIV viral load and CD4 count - as well as a sputum for smear and microbiology. The results of these tests will be made available for the clinician in charge of the patient in the National Program.

2. Participants who have failed to achieve viral suppression (<250 copies/ml) will be offered to have an HIV genotypic resistance test performed in order to help clinician to propose an adapted ART second line.
3. All participants who give consent will participate in the pharmacogenomics sub-study.

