#### 5.9 Pharmacokinetic analysis:

On each series of drug plasma concentrations, the following pharmacokinetic parameters will be determined, using the software package WinNonLin (Pharsight Corporation, California).

- Area under the curve for plasma concentration vs. time, until the last sampling time after dosing (AUCt)

- Peak plasma concentration ( $C_{\max}$ )
- The trough plasma concentration at the last time of sampling, immediately before the next dose.
- Time to peak plasma concentration ( $T_{\max}$ ).
- Half-life ( $T_{1/2}$ ).

The PK measures will be summarized using parametric or nonparametric methods (as appropriate). For RBT, the results from PK1 will be compared to PK2 and PK3, respectively. PK2 and 3 will be compared for all the drugs. The significance of differences between the pharmacokinetic measures will be determined using the Student t-test (parametric data) and the Wilcoxon signed rank test (nonparametric data). Bioequivalence analysis will be conducted using ANOVA for the AUC and  $C_{\max}$  values. The geometric mean ratios and their 90% confidence intervals will be reported. In addition the inter-individual and intra-individual variability will be evaluated for the PK measures. No interim PK analyses are planned. In addition, potential polymorphisms in specific enzymes involved in drug metabolism will be investigated.

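### Section 5.9 does not name the pre-ART rifabutin AUC (PK1) as a covariate for the between-sequence comparisons promised in Section 4, and one of its two named tests does not fit independent groups

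*Protocol*

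**What the plan says.** Section 4 (Sample size) sets the basic size from a with-versus-without-ARV comparison: "a sample size of 12 participants has a power of 80% to detect a 20% difference between the mean" AUC of the two conditions. It then explains the larger enrolment. The first reason is attrition: "To provide a target of 12 evaluable patients in each arm (24 patients in total", which leads to "we propose a maximum of 32 patients may be enrolled (16 per arm". The same paragraph adds that the extra subjects will permit a "comparison of pharmacokinetic parameters between patients initiating high dose RBT with those initiating low dose RBT" and will give enough power for a sequence effect. It attaches no effect size, SD or power figure to either use.

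Section 5.9 (Pharmacokinetic analysis) compares PK1 with PK2, PK1 with PK3, and PK2 with PK3. Significance is to be "determined using the Student t-test (parametric data) and the Wilcoxon signed rank test (nonparametric data". It also names an ANOVA for AUC and Cmax under bioequivalence without listing its terms, and says "The geometric mean ratios and their 90% confidence intervals will be reported". No covariate is named, and PK1 appears only as the within-patient reference.

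On timing, Section 5.4 says: "After completion of PK1 analysis, all participants will commence their randomized RBT-ART combination according to prior randomization". Section 2.1 has all patients on the same rifabutin dose up to PK1, and Table 3 schedules rifabutin sampling at PK1 in both arms.

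**The concern.** Comparing patients who start on the high dose with those who start on the low dose, or testing for a sequence effect, sets two independent groups of 12 to 16 patients against each other. Stable differences between patients in rifabutin handling then go into the error term, and chance imbalance between such small groups goes uncorrected. PK1 measures the same quantity in the same patients before treatment differs, so a baseline of the outcome is available at no extra cost.

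Of the two significance tests named, the signed rank test requires pairs and cannot compare the two sequence groups. Read literally, that leaves a two-sample t-test without adjustment. At stake is the precision of a secondary use of the data. The main comparison of rifabutin with and without ARV is made within patients and is unaffected.

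**Working it through.** **The plan's own figure.** Section 4 gives n = 12, 80% power and a 20% difference. It gives no SD, alpha or sidedness; the SD is left to AUC values "for RBT determined in previous studies (19". The figure therefore cannot be reproduced. Back-solving it as a paired t-test at an assumed two-sided 5% gives an SD of within-patient differences of 22.5% of the mean. That value is possible, so the figure is neither confirmed nor refuted. No power figure for the between-sequence comparison exists to reproduce.

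**Inputs for the check**
- n per arm: 12 (evaluable target) or 16 (maximum enrolled), from Section 4.
- Alpha: two-sided 5%, assumed.
- ρ, the correlation of a patient's log PK1 value with the log on-ART value: not given; range 0.3 to 0.7 assumed.

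**Formulas**
- Unadjusted: noncentral t with df = 2n − 2 and noncentrality d·√(n/2), where d is the difference in between-patient SDs.
- Adjusted for PK1: the residual SD is multiplied by √(1 − ρ²), so the noncentrality becomes d·√(n/2)/√(1 − ρ²), with df = 2n − 3.

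**Check 1: an effect with exactly 80% unadjusted power.** This needs d = 1.20 at 12 v 12 and d = 1.02 at 16 v 16. At 12 v 12 and ρ = 0.5, the residual variance falls by 25% and the noncentrality rises from 1.197 × √6 = 2.93 to 2.93/√0.75 = 3.38.

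| ρ | Adjusted power, 12 v 12 | Adjusted power, 16 v 16 |
|---|---|---|
| 0 | 79.8% | 79.9% |
| 0.3 | 83.4% | 83.5% |
| 0.4 | 86.2% | 86.3% |
| 0.5 | 89.7% | 89.8% |
| 0.6 | 93.7% | 93.8% |
| 0.7 | 97.4% | 97.5% |

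The gain is about 3 points at ρ = 0.3, 10 at 0.5 and 17 at 0.7. The loss at ρ = 0 is about 0.2 points or less.

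**Check 2: a 20% between-group difference, using the SD implied by the paired reading.** Assuming equal SDs on the two occasions, between-patient SD = 22.5%/√(2(1 − ρ)). This gives 19.0%, 22.5% and 29.1% at ρ = 0.3, 0.5 and 0.7.

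| ρ | 12 v 12, unadjusted → adjusted | 16 v 16, unadjusted → adjusted |
|---|---|---|
| 0.3 | 69% → 73% | 82% → 85% |
| 0.5 | 55% → 67% | 68% → 80% |
| 0.7 | 36% → 62% | 47% → 75% |

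On this reading the claim of adequate power for a sequence effect is doubtful without adjustment, except at low ρ with all 32 patients retained. Adjustment recovers part of the shortfall.

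**Check 3: the raw dose contrast at PK2.** Weekly doses are 7 × 150 = 1050 mg and 3 × 150 = 450 mg, a ratio of 2.33. Assume exposure follows weekly dose and the between-patient CV is 40%. The log SD is then √ln(1.16) = 0.385 and d = ln(2.33)/0.385 = 2.20. Unadjusted power is already 99.9% at 12 v 12, so adjustment adds almost nothing. The gain becomes material only at a large CV: at 80% and ρ = 0.5, power rises from 91% to 97% at 16 v 16.

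**The case against.** The strongest reply is that the protocol never assigns a test to the between-sequence comparison. Section 4 names it without a method, and the listed contrasts in Section 5.9 are within-patient, where the signed rank test is appropriate. The ANOVA's terms are unlisted, and model terms for a supplementary comparison are often left to a statistical analysis plan, which is not available here. A reader might infer that the protocol prescribes an unadjusted test or rules PK1 out. The text does not support that: it only fails to name PK1. What stands is that Section 5.9 does name its significance tests, and one of them cannot serve a comparison that Section 4 promises.

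A reader might also infer that the extra patients are enrolled for this comparison. Attrition is the first reason given; the comparison is an added use, and if losses are as feared only 12 per arm remain.

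A reader might further take a loss of about 10 points of power as established. It needs ρ near 0.5 and an effect with 80% unadjusted power, and the protocol gives neither. The correlation could be weak, because PK1 is taken without LPV/r and at another dose. That objection limits the benefit but adds no real cost.

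Finally, for the raw dose contrast at PK2 the gain is probably negligible, and the crossover estimates that contrast within patients anyway. PK1 adjustment is also unavailable for lopinavir, which is not sampled at PK1. Both points stand and limit the scope.

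**Conclusion.** The point holds as a low-severity efficiency improvement. The protocol promises between-patient comparisons, names one test that does not fit them, and does not name as a covariate a baseline scheduled for every patient. Section 1.4 places randomisation on the day of enrolment, while the Detailed Summary places it after PK1. On either reading PK1 precedes any difference in treatment, so it is a valid covariate.

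The size is conditional. An effect with 80% unadjusted power would have about 83%, 90% or 97% power at an assumed ρ of 0.3, 0.5 or 0.7 (two-sided 5%, also assumed). Under the SD implied by the planning figure, the gain for a 20% difference runs from about 3 to 28 points at 16 per arm over the same range of ρ. The benefit lies in the sequence effect and in modest differences.

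**What to change.** In Section 5.9, state that between-sequence comparisons of rifabutin AUC and Cmax (high-dose-first v low-dose-first at PK2, and any sequence effect over PK2 and PK3) use a linear model on the log scale. Its terms are sequence and the patient's own log PK1 value of the same parameter, and the result is an adjusted geometric mean ratio with its 90% CI. Add that any nonparametric comparison of independent groups uses a rank-sum test, with the signed rank test kept for within-patient contrasts. State that between-sequence comparisons of lopinavir stay unadjusted.

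The cost is a few lines of text and one degree of freedom. No new samples, visits or patients are needed. It would be best written before the pharmacokinetic data are analysed.

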### **5. Investigational plan:**

#### **5.1 Trial preparation:**

An initial preparative period of 4 months is planned for submission of the amended protocol to the ad-hoc institutions in Vietnam for approval (i.e. the Institutional Review Board and Ethical Review Committee at

PNTH, the Health Department of HCMC and the Ministry of Health of Vietnam). In parallel, additional staff will be recruited as appropriate, and all staff participating in the study will receive appropriate training (/re-training). This period will be used to prepare and print the Case Report Forms (CRF), draft the Standard Operating Procedures (SOP), and order and deliver drugs to the qualified pharmacist at Pham Ngoc Thach Hospital.

## 5.2 Trial Schedule

After this initial set-up, recruitment will be started and completed in 6 months. It is envisaged that an average of 5 patients per week will be a feasible recruitment rate. Follow up of patients will be until 2 weeks after tuberculosis treatment. The full PK analyses will be carried out after the PK3 day has been done for the last patient recruited, which will be approximately month 12 of the study, leaving four months for completion, writing up and publication (see table 2).

**Table 2: Trial Schedule**

|                                                  | Screening | Visit 1 | Visit 2        | Visit 3 | Visit 4 | Visit 5              |
|--------------------------------------------------|-----------|---------|----------------|---------|---------|----------------------|
|                                                  | Day -2    | Day 0   | Week 2         | Week 5  | Week 8  | Week 24  |
| Patient Information                              | X         |         |                |         |         |                      |
| Informed Consent                                 | X         |         |                |         |         |                      |
| Inclusion/Exclusion                              | X         | X       |                |         |         |                      |
| Randomisation                                    |           | X       |                |         |         |                      |
| Clinical History                                 | X         |         |                |         |         |                      |
| Physical examination                             | X         | X       | X              | X       | X       | X                    |
| Adverse Event Screening                          |           | X       | X              | X       | X       | X                    |
| Karnofsky score                                  | X         |         |                |         |         |                      |
| CD4 Count                            | X         |         |                |         |         | X                    |
| HIV antibody test                                | X         |         |                |         |         |                      |
| HIV viral load                       |           |         | X              |         |         | X                    |
| FBC                                  | X         |         | X              | X       |         | X                    |
| U and E                              | X         |         |                |         | X       |                      |
| LFT                                  | X         |         | X              | X       | X       | X                    |
| Amylase                              | X         |         |                |         | X       |                      |
| Pregnancy Test                                   | X         |         |                |         | X       |                      |
| Urinalysis                                       | X         |         |                |         | X       |                      |
| Chest X-ray                                      | X         |         |                |         | X       | X                    |
| Sputum Smear and Culture                         | X         |         |                |         | X*      | X                    |
| Susceptibility Testing                           | X         |         |                |         |         | X                    |
| Pharmacokinetic analysis                         |           |         | PK1            | PK2     | PK3     |                      |
| Optional Pharmacogenomics sampling   |           |         | X  |         |         |                      |
| Start Rifabutin/INH/Ethamb/PZA                   |           | X       |                |         |         |                      |
| Stop Rifabutin/INH/Ethamb/PZA & start Rifamp/INH |           |         |                |         | X       |                      |
| Start D4T/3TC-LPV/rtv                            |           |         | X              |         |         |                      |
| Stop LPV/rtv & start Efavirenz                   |           |         |                |         | X       |                      |
| Stop Rifamp/INH                                  |           |         |                |         |         | X                    |

1, 2, 3. The tests included are listed in section 1.2. The volumes of blood required for each set of tests are FBC: 4ml, Biochemical tests: 4ml, CD4 count: 4ml, Viral load: 8ml;

Pharmacogenomics (optional and for patients who give specific consent): 8ml

last visit can be done between week 24 and week 26.

\* Sputum smears in smear-positive PTB patients

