### Pharmacogenomics

There is considerable inter-individual variability in the disposition of drugs, and at least some is caused by polymorphisms in genes coding for drug-metabolizing enzyme and transporters. Some recent reports confirmed the need of pharmacogenetic studies to elucidate the ethnic or racial differences in drug disposition (pharmacokinetics - PK) which can occur at any step of drug disposition, absorption, distribution, transport, metabolism or excretion, drug-drug interactions and drug effect or tolerance, and pharmacodynamics (Haas, 2005, Telenti and Zanger, 2008). Any increase or decrease in drug concentrations and exposure will impact on efficacy and tolerance. The present pharmacogenetic sub-study could be helpful for a better understanding of variability in rifabutin or antiretroviral PK and of occurrence of adverse events in co infected tuberculosis and HIV Vietnamese patients included in the ANRS12150b study who accept to participate in this sub-study.

The objective of the present study is to identify in the included population single base mutations (Single Nucleotide Polymorphism SNPs) within genes involved in drug metabolism and transport. This will allow identification of patients carrying allelic variants encoding for loss of function enzymes or transporters. The SNPs will be selected according to the literature and the SNP database. The frequency of SNPs varies between populations.

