Rifamycins (rifampicin and rifabutin), are well known for their ability to induce drug-metabolizing enzymes and transporters, although rifabutin to a lesser extent, through activation of a nuclear receptor: the Pregnane X Receptor (PXR). It is now accepted that drug-dependent induction of genes important for drug disposition is mediated by nuclear receptors pregnane X receptor (PXR) (Tirona et al. 2005, which function as key ligand-activated transcription factors that control the expression of drug metabolizing enzymes and transporters. In comparison with other genes, relatively few single nucleotide polymorphisms (SNPs) are observed in hPXR. The single amino acid variants identified in subjects of Caucasian and African origin include amino acid changes in or close to the Ligand Binding Domain (R122Q (PXR\*4), V140M, D163G, and A370T) and others in the N-terminal region (E18K, P27S (PXR\*2), and G36R (PXR\*3). The most frequent of these,

P27S, was identified in 14.9% of chromosomes from subjects of African origin, whereas the others had allele frequencies below 3%.

Our main goal is to select some “target” functional SNPs and genotype our population to identify the impact of those different genes on PK and PD variabilities. We will focus on the association between rifabutin-lopinavir/ritonavir pharmacokinetics and genetic polymorphism of CYP3A5, ABCB1, OATP1B1 and PXR genetic polymorphisms. NAT2 and GST polymorphism will be related to liver toxicity if any. Any new data on these drug pharmacogenetics or unexpected results of the pharmacokinetic/pharmacodynamic study or tolerance could lead to study other allelic variant of drug metabolizing enzymes or transporters.

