### 5.3 Recruitment procedures:

Patients who are eligible for the trial will be recruited at the Outpatient unit in Pham Ngoc Thach (PNT) Hospital, where new cases of tuberculosis are diagnosed and receive their full treatment under direct observation (see Appendix 1). The appointed clinical trial nurse and counsellor will liaise with the doctors responsible for managing tuberculosis to identify patients who have been diagnosed with pulmonary tuberculosis and HIV, who have had a CD4 count analysis. Patients will be given full information on the objectives and methods of the trial. Patients will be given a copy of the information sheet to read before the screening appointment. If, at time of screening, patients present with an intercurrent opportunistic infection requiring specific concomitant treatment, they will not be included in the study.

Patients meeting eligibility criteria after screening will be enrolled in the trial and started on 300mg RBT in combination with INH, PZA, and EMB, corresponding to day 0 of the trial (visit 1).

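### The only DNA sample is scheduled at Week 2, 14 days after tuberculosis drugs start, so patients who die or leave before that visit have no genotype for the planned genotype-toxicity analysis

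*Protocol*

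**What the plan says.** Table 2 has one row for genetic sampling, "Optional Pharmacogenomics sampling", marked only in the Visit 2 (Week 2) column. Its footnote reads "Pharmacogenomics (optional and for patients who give specific consent): 8ml". The same table starts rifabutin, isoniazid, ethambutol and pyrazinamide at Visit 1 (Day 0) and marks informed consent at screening only. Section 5.4 confirms the interval: "After fourteen days of RBT therapy, patients will return and will undergo the" first PK assessment.

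The Pharmacogenomics part of Section I gives the sub-study two purposes. It is to support a "better understanding of variability in rifabutin or antiretroviral PK and of occurrence of adverse events", and it commits to a specific toxicity analysis: "NAT2 and GST polymorphism will be related to liver toxicity if any". The same part links NAT2 and the GST enzymes to the elimination of isoniazid.

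Section 5.10 names whole blood as the source of DNA. Section 5.11 stores plasma and microbiological samples. No earlier, unscheduled or withdrawal-visit DNA sample is described.

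**The concern.** A toxicity analysis by genotype should cover the patients exposed to the drugs in question. Isoniazid exposure starts on Day 0, but a genotype exists only for patients who reach Week 2. The genotype-toxicity part of secondary objective 5 is therefore conditioned on remaining in the trial for 14 days after exposure begins.

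An early death, or an early exit for toxicity, can be among the more informative cases for this question. Section 5.5 assesses adverse events at unscheduled as well as scheduled visits, and registers every death with an attempt to establish its cause. For such a patient the event would be on file with no genotype to set against it. Germline genotype does not change with treatment, so nothing about the measurement requires waiting, and the protocol gives no reason for choosing Week 2.

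**Working it through.** **1. Timing.** Drug start is Day 0 and the DNA sample is at Week 2, so the gap is 14 days. That is 14/56 = 25% of the eight-week intensive phase.

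**2. What each type of patient contributes under the present schedule.**

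| Course of a consenting patient | Genotype | Toxicity outcome | PK profile |
|---|---|---|---|
| Dies or leaves before Week 2 | None | Clinical reports, unscheduled visits and deaths only; no scheduled on-treatment LFT | None |
| Early toxicity, attends Week 2 | Yes | Yes, including the Week 2 LFT | PK1 at least |
| Leaves after Week 2 | Yes | Yes, up to exit | PK1 at least |

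Only the first row loses information. It loses nothing for the PK-genotype analysis, because no PK is measured before Week 2 either.

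**3. The protocol's only figure on attrition.** Section 4 expects patients who "may have high mortality and morbidity, resulting in a high attrition rate". It goes from 24 evaluable to a maximum of 32 enrolled. The implied loss is 1 − 24/32 = 25%, and 24/(1 − 0.25) = 32 reproduces the total. The 25% is back-calculated, since the section states neither a rate nor when losses occur.

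**4. Expected number without DNA.** Let d be the assumed probability of loss before Week 2, with all 32 patients consenting and losses independent. Expected number missing = 32 × d. Chance of at least one = 1 − (1 − d)^32.

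| Assumed d | Expected missing of 32 | Chance of at least one |
|---|---|---|
| 3% | 0.96 | 62% |
| 5% | 1.6 | 81% |
| 10% | 3.2 | 97% |
| 12.5% | 4.0 | 99% |

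**5. Link between d and the implied 25%.**
- Constant hazard over 8 weeks: d = 1 − 0.75^(2/8) = 6.9%, about 2.2 patients.
- Constant hazard over 24 weeks: d = 1 − 0.75^(2/24) = 2.4%, about 0.8 patients.
- Half of the 8 losses before Week 2: d = 4/32 = 12.5%, 4 patients.

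The range of about 1 to 4 patients covers these cases. With sampling before the first dose, the number missing for this reason is zero under every assumption.

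**The case against.** The strongest counter-argument is that little liver information is lost. After screening, the next scheduled LFT is also at Week 2, so an earlier DNA sample would mostly add genotypes without a scheduled liver outcome. This stands and narrows the point to clinically reported events and deaths. It does not remove it, because Section 5.5 records those events.

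Second, the stated focus of the sub-study is PK, the NAT2/GST analysis depends on liver toxicity occurring at all, and antiretrovirals start only at Week 2, so the combined-treatment phase begins at the time of the sample. That is fair as to emphasis. But NAT2 and GST are brought in because of isoniazid, which starts on Day 0.

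Third, Week 2 has practical merit. Patients are admitted and sampled repeatedly for PK1, so the DNA sample adds little burden there. Section 5.10 also allows genome-wide screening, which makes it defensible to collect DNA only from patients who reach the PK phase. Eligibility excludes grade 3 or 4 findings, LFT above grade 2, Karnofsky below 80% and concomitant opportunistic infection needing treatment, which plausibly limits early loss. These points bear on size and cost, and they stand.

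Three stronger readings are tempting and are not supported:
- A reader might infer that Section 5.4 ("All participants who give consent will participate in the pharmacogenomics sub-study") is contradicted by the schedule. The sentence makes participation depend on consent, the sample needs its own consent, and the text available does not date that consent. It could be sought at Week 2.
- A reader might infer that Week 2 is the heaviest blood-draw visit and should be relieved for that reason. With the Section 5.8 volumes (5 ml for rifabutin alone, 8 ml with antiretroviral assay), Week 5 PK sampling is 8 × 8 + 5 = 69 ml, or 74 ml with a 48-hour sample. Adding 8 ml for FBC and biochemistry gives 77 to 82 ml. Week 2 comes to 45 to 50 ml for PK plus 4 + 4 + 8 + 8 = 69 to 74 ml.
- A reader might infer that the association is necessarily pulled towards no effect. The protocol gives no basis for a direction.

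**Conclusion.** The point holds as a small improvement to the schedule. Sampling at Week 2 selects the genotype-toxicity population on having stayed in the trial for 14 days after exposure starts, and no alternative source of DNA is described. The number affected is about 1 to 4 of 32. That rests on an assumed early loss of 3% to 12.5%, on all 32 patients consenting, and on genetic consent being available before Week 2. How many of those patients would have a toxicity event cannot be derived from the protocol. The analysis is optional and would rest on few events in any case, so the gain is a complete denominator and possibly one or more informative cases. The primary PK objective and the PK-genotype analysis are unaffected.

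**What to change.** In Table 2, move the mark for optional pharmacogenomics sampling from Visit 2 to Visit 1, before the first dose. Alternatively, take the 8 ml with the screening bloods and discard it if the patient is not enrolled. State that the specific genetic consent is obtained at screening. Analyse toxicity by genotype in all consenting enrolled patients, and PK by genotype in those with PK profiles.

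The cost is one venepuncture at Day 0, where Table 2 lists no blood test, or 8 ml on top of the roughly 25 ml at screening (about 33 ml in all). DNA would also be held from a few patients who never reach PK1. No new type of assay, staff or patients is needed, and no treatment or clinical rule changes.
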